## Abstract

**Background:**

There is an increasing amount of evidence for the effectiveness of rehabilitation interventions for people with severe mental illness (SMI). In the Netherlands, a rehabilitation methodology that is well known and often applied is the Comprehensive Approach to Rehabilitation (CARe) methodology. The overall goal of the CARe methodology is to improve the client’s quality of life by supporting the client in realizing his/her goals and wishes, handling his/her vulnerability and improving the quality of his/her social environment. The methodology is strongly influenced by the concept of ‘personal recovery’ and the ‘strengths case management model’. No controlled effect studies have been conducted hitherto regarding the CARe methodology.

**Methods/design:**

This study is a two-armed cluster randomized controlled trial (RCT) that will be executed in teams from three organizations for sheltered and supported housing, which provide services to people with long-term severe mental illness. Teams in the intervention group will receive the multiple-day CARe methodology training from a specialized institute and start working according the CARe Methodology guideline. Teams in the control group will continue working in their usual way. Standardized questionnaires will be completed at baseline (T0), and 10 (T1) and 20 months (T2) post baseline. Primary outcomes are recovery, social functioning and quality of life. The model fidelity of the CARe methodology will be assessed at T1 and T2.

**Discussion:**

This study is the first controlled effect study on the CARe methodology and one of the few RCTs on a broad rehabilitation method or strength-based approach. This study is relevant because mental health care organizations have become increasingly interested in recovery and rehabilitation-oriented care.

**Trial registration:**

The trial registration number is ISRCTN77355880.

## Background

People with serious mental illnesses (SMI) experience numerous problems in their daily lives. Studies on employment, for instance, show that about 10–20 % of people with SMI have regular paid employment, 50 % work as volunteers or participate in organized day activities and approximately 40 % have no paid or unpaid employment at all [1, 2]. Furthermore, a lack of social contacts and loneliness is common among people with SMI [3–5]. Previous studies show that these people experience unmet needs in these areas, which results in a lower quality of life [6–9]. Hence, it is important that mental health care organizations address these needs and wishes. Psychiatric rehabilitation practices have been applied by mental health care organizations to increase social participation and improve quality of life over the last two decades [10, 11]. The goal of these practices is ‘to help individuals with complex, longer term mental health problems to develop the emotional, social and practical skills needed to live, learn and work in the community with the least amount of professional support’ [11–13]. Psychiatric rehabilitation is closely related to the concept of personal recovery. Personal recovery implies a client-oriented definition of recovery in which the emphasis lies more on personal development and growth than on symptom reduction. Important aspects of recovery are: hope, empowerment and the feeling of living a satisfying life despite symptoms of illness [14–22]. While recovery is an individual and subjective process, mental health care organizations can be recovery-oriented. The recovery of clients with SMI can be supported by, among other things, providing psychiatric rehabilitation services [11, 23].

Several rehabilitation methods have been developed to help people identify and achieve their own individual goals, including living independently, self-care, gaining and staying in employment, participating in routine educational settings, developing better relationships with their families, and pursuing leisure activities [24–27]. Comprehensive methods exist which focus on the personal goals and wishes of clients. Examples of well-known comprehensive rehabilitation methods are the Boston Psychiatric Rehabilitation (PR) approach [12] and the strengths model [28]. There are also rehabilitation methods which focus on a specific aspect of life, for example, ‘Individual Placement and Support’ (IPS) in which people are supported to gain and stay in competitive employment [29]. Finally, there are methods that aim at improving cognitive functioning or practical skills, e.g., cognitive remediation [30, 31] and cognitive adaptation training (CAT) [32, 33].

Internationally, there is an increasing amount of evidence for the effectiveness of the aforementioned interventions on social functioning [11, 13, 25, 26, 29, 34]. Swildens and colleagues [35] found that, among clients who participated in the Boston PR approach, goal attainment and social functioning were significantly higher compared with clients in the control condition. Furthermore, IPS has a strong effect on vocational outcomes [29, 36, 37]. The strengths model is associated with positive results on different outcomes [38–40] including decreased hospitalization and improved quality of life and social functioning [39, 41]. Although research on rehabilitation methods thus shows promising results, their effectiveness remains largely unknown. For example, few randomized controlled trials (RCTs) have been conducted to research the strengths model [38, 42], and most of these studies had methodological limitations such as small sample sizes and inadequate randomization [38]. Furthermore, in most of the studies only the effects on social functioning and quality of life were studied. Effects on personal recovery, hope and empowerment were not investigated, although these are also seen as an important outcome in mental health care nowadays. Finally, little is known about the effectiveness of these rehabilitation-oriented practices for clients of sheltered and supported housing facilities [43].

In the Netherlands, a rehabilitation method that is well known and often applied in mental health care is the Comprehensive Approach to Rehabilitation (CARe) methodology. The overall goal of the CARe methodology is to support a client in his/her recovery and to improve his/her quality of life. The central principles of this approach are: realizing goals and wishes; handling vulnerability; and improving the quality of the client’s social environment [44, 45]. The methodology is strongly influenced by the concept of ‘personal recovery’ and by the strengths model [28]. The CARe methodology is used in several mental health care organizations and organizations for sheltered and supported housing. It is suitable for all clients who experience psychosocial problems, regardless of the severity of their impairments or the phase of their recovery process. With regard to the CARe methodology, in contrast with the Boston PR approach, no controlled effect studies have yet been carried out [46, 47]. In the Netherlands, people with SMI often receive care from both mental health care organizations and housing facilities. Central in the approach of housing facilities is the focus on rehabilitation of their clients, while mental health care organizations focus more on treatment [43]. Several of these housing facilities make use of the CARe Methodology; therefore we chose these as research sites for this study.

This is, to our knowledge, the first RCT on the effectiveness of a method that combines rehabilitation, recovery and strengths principles. Finally, the CARe methodology is distinct from other methods due to the fact that it can be used for even the most vulnerable clients and not only the motivated ones. Hence, the aim of this study is to investigate the effectiveness of the CARe methodology on recovery, social functioning, quality of life, hope, empowerment, self-efficacy beliefs and needs for care of people with SMI.

## Methods/design

In this article, we follow the Consolidated Standard of Reporting Trials (CONSORT) 2010 statement on extension of the standard to cluster trials [48].

### Study design

This study is a two-armed cluster RCT that will be executed in teams selected from three organizations for sheltered housing in the Netherlands. These teams all provide sheltered housing and/or supported independent living services. Randomization will be applied at team level and will be stratified by organization. The professionals of the teams in the intervention group will receive a basic training in CARe methodology (three full-day meetings and four half-day meetings; see ‘Intervention’ for further information) while teams in the control group will continue to offer ‘care as usual’. Cluster randomization is necessary because the intervention is offered at team level; reorganization of this structure (i.e., reassigning clients to other teams in case of individual randomization) would disturb the clients’ living situations and relations of trust with their personal key workers, and would therefore be ethically undesirable. Furthermore, cluster randomization reduces contamination between the trial arms as much as possible. However, we will not be able to prevent staff changes completely; therefore we shall monitor this and take this into account in the analysis (see paragraphs outcome measures and statistical analysis). The participating teams will be randomized on an equal basis so an equal amount of teams and clients can participate in both arms. An independent researcher of the Department of Methodology and Statistics of Tilburg University will perform the randomization. The professionals and researchers will be aware of the allocation to the conditions; clients cannot be blinded but it will not be pointed out to them explicitly which condition they are in. All clients in the participating teams will be asked to participate in the study through an informed consent procedure. Standardized questionnaires will be completed at baseline (T0), and at 10 (T1) and 20 months (T2) post baseline (see Fig. 1). Besides client outcomes, the model fidelity of the CARe methodology will be assessed at T1 and T2.

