### Setting

The organizations for sheltered and supported housing in which this study is conducted provide ‘sheltered housing’ and ‘supported independent living’ services. In sheltered housing facilities, people with SMI live together and receive daily supervision from care professionals. In the case of supported independent living, the client lives independently, alone or with family or friends, and receives a certain amount of care at home. Both sheltered housing and supported independent living services are often provided by the same team of professionals. In that case the home base of the team is a sheltered housing facility, from where the team also provides supported independent living services to clients in the same area. The teams consist of ‘key workers’ and ‘support workers’. Key workers coordinate care around a client and draw up support plans and direct the execution of these plans. Support workers support clients in their daily living and are responsible for the execution of (parts of) the support plan. Furthermore, support workers take care of the living environment in a sheltered housing facility. Generally, key workers and support workers are educated as social workers or nurses. The teams are not responsible for the medical/psychiatric treatment of their clients. Most clients receive treatment from external (multidisciplinary) treatment teams from mental health care organizations.

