#### Team inclusion criteria

Teams of three organizations for sheltered and supported housing facilities in the Netherlands will be included. These teams provide sheltered housing and/or supported independent living services to adults with severe mental health problems. These teams work according to an outdated form of the CARe Methodology. Furthermore, in these teams the (outdated) CARe Methodology is not adopted by the workers or is inadequately applied.

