### Power calculation/sample size

Sample size was calculated taking into account the design effect (due to group randomization) and the expected effect size. The measures with the highest expected effect size within the duration of the study of 20 months are: empowerment (0.38) and hope (0.50) [26, 43]. Cohen’s d was used as the measure for effect size with *α* = 0.05 and a power of 0.80, based on a two-sided test. The design effect used is estimated to be 1.5 based on an average cluster size of 38 and an intra-cluster correlation (ICC) of 0.013. Based on the effect size of empowerment (0.38; the lowest of the two above mentioned) a sample of 128 clients per condition is needed. When taking into account a reduction of 20 % for loss due to follow up, 160 clients per group will be recruited to achieve the required power. To reach a sufficient amount of clients 16 teams will be included in the study, which together provide services to 890 clients.

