### Statistical analysis

Data will be analysed according to intention-to-treat, meaning that participants will be analysed in the group to which they were allocated by randomization [65]. SPSS 19 will be used for the analysis. Because the study has a cluster randomized design, longitudinal multilevel analysis (linear mixed modeling with random intercepts at both team level and individual level) is the analysis method of choice. First, effectiveness of the CARe Methodology on the three primary outcomes, recovery, social functioning and quality of life, will be evaluated. Subsequently, the effectiveness on four secondary outcomes, hope, empowerment, self-efficacy beliefs and need for care will be evaluated. An alpha correction (i.e., Bonferroni adjustment) will be applied across analysis of the primary measures in order to maintain a family-wise alpha level of 0.05. A separate Bonferroni adjustment will be applied to the set of analysis for the secondary measures to maintain their family-wise alpha level at 0.05. Furthermore, in separate analyses we will assess whether different types of predictors explain the outcomes: (1) client characteristics (age, gender, having a partner, type of housing, diagnosis), (2) symptom severity (BSI), (3) health and day care utilization. Only predictors that influence the prediction of the outcome measures will be added tot the final model. Outcomes will be measured at 10 months and 20 months post-baseline (time will be analyzed as a categorical variable).

To detect significant differences in the baseline characteristics between the intervention group and control group descriptive analysis will be used. When necessary these differences will be taken into account in the analysis. Missing data and drop-outs will be analysed and accounted for by multiple imputation if the assumption of data missing at random (MAR) is not violated [66].

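### Stratifying 16 teams by organisation alone balances the number of teams, not the number of clients or the housing mix, and adjustment for housing type is left to data-driven rules

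*Protocol article*

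**What the plan says.** The Study design section of the protocol article gives the allocation rule and what it is meant to achieve: "Randomization will be applied at team level and will be stratified by organization", and "The participating teams will be randomized on an equal basis so an equal amount of teams and clients can participate in both arms". An independent methodologist carries out the randomisation. No balancing on team size or type of service is mentioned.

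The teams are not uniform in what they offer. Team inclusion criteria: "These teams provide sheltered housing and/or supported independent living services to adults with severe mental health problems". The Setting section describes sheltered housing as communal living with daily supervision, and supported independent living as living in one's own home with some care. It adds: "Both sheltered housing and supported independent living services are often provided by the same team of professionals".

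Power calculation/sample size says that "16 teams will be included in the study, which together provide services to 890 clients". It gives neither the size of each team nor the number of teams per organisation.

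Statistical analysis lists candidate predictors that include "client characteristics (age, gender, having a partner, type of housing, diagnosis". They enter the final model only if they turn out to influence the outcome. Differences between the arms at baseline are taken into account where that is judged necessary.

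**The concern.** The sentence in Study design infers equality of clients from equality of teams. That inference fails unless the teams are about the same size, which the article does not say. The same gap applies to who the clients are. A team may serve sheltered clients, independent clients or both, and nothing in the stated method spreads that mix evenly.

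With 16 teams, chance leaves more room for imbalance than with many small units. Housing type is the characteristic to watch, because the authors themselves name it as a possible predictor and because a primary outcome, the Social Functioning Scale, has two independence domains. If the arms come out visibly different on housing, the stated remedy is a choice made after the data are seen, in an open trial whose researchers know the allocation. At stake are some precision and the ease with which a reader can accept the result.

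**Working it through.** The plan gives no figure for balance, so there is none to reproduce on that point. The check has four steps.

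**1. What the stated rule fixes.** Inputs from the article: 16 teams, three organisations, 890 clients served (890/16 = 55.6 per team on average). The number of teams per organisation is not given, so 6/6/4 and 8/4/4 are assumed.
- Allocations equal within organisation, 6/6/4: C(6,3) × C(6,3) × C(4,2) = 20 × 20 × 6 = 2,400.
- For 8/4/4: C(8,4) × C(4,2) × C(4,2) = 70 × 6 × 6 = 2,520.

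Every one of these has equal numbers of teams per arm. None is constrained on clients or housing.

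**2. How large the imbalance could be.** Team sizes were drawn from a gamma distribution scaled to 890 and team sheltered shares from a beta distribution; all admissible allocations were then compared. The spreads are assumptions.

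| Team-size CV | SD of sheltered share | Mean difference, clients | Mean difference, share | Share differs by >20 points |
|---|---|---|---|---|
| 0.2 | 0.1 | 36 | 4 points | 0% |
| 0.3 | 0.22 | 53 | 9 points | 8% |
| 0.5 | 0.34 | 88 | 15 points | 29% |

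The results hardly depend on which strata are assumed. Restricting the draw to the best-balanced 10% of allocations brings the mean differences down to about 9 to 23 clients and 1 to 4 points, with essentially none above 20 points.

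**3. What unequal client numbers cost.** Inputs from the article: d = 0.38, two-sided α = 0.05, design effect 1.5, 128 per arm (256 in total). Power = Φ(d/SE − 1.96), where SE = √(1/m₁ + 1/m₂) and m is the arm size divided by 1.5.
- 50:50: m = 128/1.5 = 85.3 in each arm, SE = 0.153, power 0.699.
- 55:45: power 0.695.
- 60:40: m = 102.4 and 68.3, SE = 0.156, power 0.682.

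The baseline is 0.699, not the stated 0.80, because 128 per arm matches a one-sided calculation (85.63 × 1.5 = 128.4) although the article says two-sided. That is a separate matter; only the fall from 0.699 counts here, and it is small. The largest mean gap, 88 clients, is 489 against 401 served, or 55:45. The smaller arm would then need 160/401, about 40%, to take part in order to meet its recruitment target.

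**4. What uneven housing mix could do to the contrast.** With a total outcome SD of 1 and the stated ICC of 0.013, the between-team SD is √0.013 = 0.114. Suppose, as an upper case, that sheltered share explains all of it. Then shift = 0.114 × (difference in share)/(SD of share):
- 0.114 × 0.04/0.1 = 0.046
- 0.114 × 0.09/0.22 = 0.047
- 0.114 × 0.15/0.34 = 0.050

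So the shift is about 0.05 SD on average, before any adjustment, against a planned effect of 0.38. A 20-point difference would give 0.114 × 0.20/0.34 = 0.067 to 0.114 × 0.20/0.22 = 0.104. This assumes that the stated ICC applies to the outcome in question.

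**The case against.** The case on the other side is substantial.

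- **Stratified allocation by an independent person is a legitimate design.** Chance imbalance under it is not bias, and the team-level random intercept and the design effect already allow for variation between teams. This stands.
- **The article says that equal numbers of clients can take part, not that they will.** The pool of 890 is large against 160 per group, and an uneven split costs almost no power. This stands, and it makes client count the lesser part of the point.
- **The size of the imbalance rests on assumed spreads.** Mixed teams, which the Setting section calls common, push towards the low row of the table, where no allocation exceeds 20 points. This stands; the range is shown for that reason.
- **The plan already has mitigation.** All outcomes are measured at T0, housing type is a candidate covariate, and baseline differences may be adjusted for. This stands in part. T0 measurement deals with differences in level but not with any difference in change over 20 months. The other two depend on rules applied after the data are seen, with no fixed criterion.

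A reader might go further and infer that the arms would hold populations with different expected courses. The article does not say so: it describes different living and supervision arrangements and treats housing type as a possible predictor. A reader might also infer that housing can be adjusted for only with a handful of team-level units. That does not follow either, because in mixed teams housing type varies between clients of the same team, and the article classes it as a client characteristic.

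**Conclusion.** The point holds in a limited form. The stated method delivers equal numbers of teams; the claim of equal numbers of clients does not follow from it, and housing mix is not balanced by design. Under the assumed spreads the arms would differ on average by about 36 to 88 clients and 4 to 15 percentage points in sheltered share, with differences above 20 points in 0% to about 29% of allocations. The true figures need per-team data that the article does not give.

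The consequence is modest: a fall in power from 0.699 to 0.682 even at a 60:40 split, and an average shift of about 0.05 SD before adjustment if the ICC of 0.013 holds and housing explains all variation between teams. It would be wrong to conclude that the design is biased or that housing imbalance is likely to mimic or conceal an effect of the size planned for. What remains is an inaccurate sentence, an inexpensive balancing step not taken, and a covariate choice better fixed in advance.

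**What to change.** Before randomisation:

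- Keep stratification by organisation. Have the independent researcher list the allocations that are equal within organisation, score each on the difference between arms in clients served and in share in sheltered housing, and draw at random from the best-balanced set. Taking the best 10% leaves 240 of 2,400 allocations for 6/6/4 or 252 of 2,520 for 8/4/4, so a real random draw remains.
- Pre-specify the client's housing type at T0, which the trial already collects, as a fixed covariate in the primary models, in place of the rule that admits it only if it proves predictive.

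If randomisation is already done, correct the sentence in Study design so that it claims equal numbers of teams only, report clients and housing mix by arm, and fix the housing covariate before outcomes are analysed.

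The cost is a short script and per-team caseload and housing counts, which the organisations should be able to supply, though the article reports only the total. The drawbacks are fewer admissible allocations, and balancing variables that must be settled beforehand and carried into the analysis.
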